### **(a) Background of research**

There is strong evidence that regular physical activity (PA) is associated with a range of physical health benefits for school-age youth, including improvements in body composition, physical capacity, and overall health-related indicators (e.g., blood pressure, insulin resistance, lipid profile) [1]. Emerging evidence also suggests that PA and physical fitness have a positive effect on mental health [2], cognitive function and academic performance [3]. Executive functions are generally defined as “high-level cognitive processes” that manage other basic cognitive functions [4]. They consist of functions such as planning, self-regulation, initiation and inhibition, and cognitive flexibility [5, 6]. These functions are believed to be important prerequisites for successful learning in preadolescent children [7], predict better health and wealth, and has been associated with a reduced likelihood of being convicted of a criminal offence [8]. Several recent meta-analyses have suggested that PA may positively affect cognition and executive function in children [9, 10]. Despite the known benefits of an active lifestyle, more than half of Hong Kong’s children and young people fail to follow the current physical activity recommendations [11], and trends show a decline in health-related physical fitness [12]. Executive functions develop from early childhood and through adolescent into adulthood [13, 14], with large developmental changes occurring during the elementary school years [15, 16]. Accordingly, effective interventions implemented early in life when the higher cortex is still developing, have the potential to elicit significant long-term improvements [17]. Therefore, it is important to find effective strategies to promote the PA of children, so as to improve their executive function during their childhood.

Attention-deficit/hyperactivity disorder (ADHD) is a commonly diagnosed developmental disorder, with a 5.3% worldwide prevalence in children and adolescents [18]. The most common symptoms include inattention, impulsivity, impaired inhibition, and hyperactivity [19]. Also, young people with ADHD are often characterized by dysfunction in high level cognitive functions such as executive function [20]. This executive dysfunction may play an important role in the commonly observed behavioral problems in children with ADHD. There are a number of ways to treat ADHD, e.g., medication, psychotherapy, psychoeducation, neuro-feedback, behavior management, etc. Of these treatments, PA and exercise have emerged as effective strategies to manage ADHD given that neither are associated with negative side effects (see recent reviews [21-24]). To summarize, although not always consistently, PA, especially moderate- to high-intensity aerobic exercise, may improve the emotion/mood, behavior, executive function, and some physical measures of children with ADHD. Acute aerobic exercise may have a positive effect on a variety of measures with a large effect size up to 1.26 in children with ADHD [23]. Two studies have reported medium-to-large effects of acute exercise on executive function [25, 26]. Long-term exercise interventions have also been shown to benefit children with ADHD, with improvements in some measures showing a large effect size up to 0.96 [23]. However, these benefits have been mainly described as an improvement of behavioral and emotional problems [22]. Several studies have reported that long-term ‘mixed exercise programs’ may have moderate to significant effects on several aspects of executive function (e.g., inhibition) and attention in children and adolescent with ADHD [27-29], but other studies did not report the same findings [30]. Therefore, so far evidence-based suggestions regarding the optimal exercise for children with ADHD remain somewhat inconsistent [22].

Research into the relationship between PA and ADHD has generally involved mixed exercise programs at a low- to moderate-intensity; running and stationary cycling have been the most common exercise modes. Whether structured PA is effective for young people is yet to be examined [31]. Children's habitual PA patterns are characterized by participation in games or "unpredictable" sports activities (e.g., football, basketball) [32]. Given that children's intrinsic motivation, or level of enjoyment, is also a strong predictor of PA participation [33], any intervention program should be designed to optimize their enjoyment of PA and thus enhance the likelihood of long-term adherence. When compared to structured exercise such as running or cycling, games-based PA arguably provides a more attractive, acceptable, sustainable and enjoyable exercise model for young children [34]. To date, only a few studies have examined the effect of an acute bout of team game-based activity on cognitive function in healthy children and adolescents [35-38]. Research has found that different aspects of cognitive function, such as free recall memory, attention, executive function, and working memory are improved following an acute bout of game-based team exercise (e.g., basketball, tennis) [35-38]. For children with ADHD, mixed exercise protocols have generally been used in intervention programs, and only a few studies have used team sport-based games as part of their exercise intervention [29-39]. However, given the design of these studies, it is not possible to distinguish the sole effect of game-based PA from those of the mixed exercise protocols in these studies. A recent study has reported that a 12-week table tennis exercise has positive effects on the gross motor skills and some of the executive function performances (mainly inhibition) in the ADHD training group, compared with the ADHD non-training group and a control group [40]. It should be noted that the game-based PA in these aforementioned studies was generally 'aerobic' in nature, and completed at low- to moderate-intensities.

Recently high-intensity interval training (HIIT) has emerged as a feasible and efficacious strategy for improving the physical health of young people [41-42]. The HIIT can be completed in a short period of time, while resulting in equivalent physiological adaptations to longer sessions of traditional aerobic training [43]. Recent research has suggested that traditional HIIT intervention programs, including running and cycling, may improve executive function in healthy children and adolescents [44-46]. It has been suggested that a very brief HIIT intervention over two weeks reduced off-task behavior and enhanced selective attention in primary school children [44-45]. For children with ADHD, to the best of our knowledge, only one recent study [47] was conducted to investigate the effect of a traditional HIIT program on physical fitness, motor skills, social behavior, and quality of life. In this randomized controlled trial, 28 boys with ADHD were assigned to either a traditional HIIT group or a standard multimodal therapy (TRAD) group. After the three-week intervention, the authors reported that HIIT was more effective in improving motor skills, self-esteem, relations with friends, competence, and subjective ratings of attention, compared with TRAD. However, despite this encouraging preliminary evidence, it remains unclear whether HIIT can be adopted to treat children with ADHD to improve their executive function, a key aspect in many facets of life.

While the limited findings regarding the effects of HIIT on executive function are encouraging, and HIIT has emerged as an enjoyable and effective exercise for children [42], previous studies have tended to prescribe HIIT interventions with a focus on running and jumping [44-46]. The effect of game-based HIIT interventions on the executive function of children have yet to be

investigated. Research of this nature is needed, particularly to determine whether game-based HIIT can improve outcomes (e.g., executive function, social behavior, sports skills, etc.) for children with ADHD.

It is also important to understand the mechanism behind the effect of exercise on the executive function of children. A number of mechanisms have already been proposed to link exercise to executive performance in children with ADHD, including brain structure and activity, neurotransmitter and neurotrophins (such as norepinephrine, dopamine, serotonin, and brain-derived neurotrophic factor), neuroendocrinology, angiogenesis, and cerebral blood flow (see review [3, 48]). It is still unclear what the exact mechanism is behind the exercise benefits, and more studies are required to explore all these possible mechanisms. In the human brain, both the frontal and subcortical regions are believed to be responsible for executive function [4]. However, it is suggested that the prefrontal cortex plays a key role in executive function [49]. Although one previous study suggested that there is improved brain activity in the prefrontal cortex in adolescent with ADHD after aerobic exercise using fMRI technology [28], related studies are quite limited. As mentioned, cerebral perfusion to the prefrontal cortex may be an important mechanism linking exercise to improved executive function, as blood flow will directly influence oxygen delivery [50]. Functional near-infrared spectroscopy (fNIRS) is a sensitive non-invasive means of estimating cerebral hemodynamic response to cognitive tasks by measuring changing levels of oxyhemoglobin (O2Hb), deoxyhemoglobin (dHb), and total hemoglobin (tHb) in the superficial layers of the cortex [51]. The fNIRS has previously been used to investigate real-time changes in cortical oxygenation following an acute bout of exercise and the results show that prefrontal oxygenation is either maintained or increased between moderate and heavy exercise intensities, but may decrease at near-extreme exercise intensities [52, 53]. However, it is not clear whether changes in executive function following a long-term exercise intervention are in fact accompanied by the changes in the cerebral hemodynamic response in the prefrontal cortex, especially for children with ADHD.

Therefore, the primary aim of the proposed study is to investigate the effect of two different kinds of exercise programs, i.e., a 12-week game-based HIIT (GameHIIT) program and a 12-week game-based structured aerobic exercise (GameSAE) program, on the executive function of children with ADHD. The secondary aim is to explore a possible mechanism behind the potential association between exercise intervention and improvements in executive function. The hypothesis of the proposed study is that both GameHIIT and GameSAE programs will significantly improve the executive function of children with ADHD, compared with those in the control group. A secondary hypothesis is that the GameHIIT group may confer additional benefits when compared with the GameSAE group.

### **Work done by us**

The research group members have completed a series of studies relating to HIIT, ADHD, or Rugby (details are provided in the attached CVs). Some pilot data have indicated that acute bout of HIIT or game-based aerobic exercise enhance the executive function of college athletes and healthy adolescents. The expertise and relevant experience of the entire research team over the past number of years will ensure that the proposed project is conducted in a systematic and efficient manner. It is anticipated that the proposed project will be completed successfully.

## **(b) (i) Research plan and methodology**

### **Participants**

A total of 42 children with ADHD will be recruited from local schools. The inclusion criteria are: (1) Chinese children aged 8-13 years; (2) a clinical diagnosis of ADHD by developmental pediatricians or clinical psychologists/psychiatrists; (3) a physician/psychologist's recommendation for participation. The exclusion criteria are: (1) diagnosed with a major neurodevelopmental or psychiatric disorders (e.g., autism spectrum disorder, intellectual disability, etc.); (2) acute/chronic diseases that may affect engagement in physical activity; and (3) a tendency to experience convulsions. Informed consent will be obtained from the school principal, parents, and study participants before the study begins. Human research ethics approval will be sought from the Human Research Ethics Committee of the University.

### **Sample Size Calculation**

The sample size is calculated using G\*Power 3.1. To elucidate the differences in the executive function tests with a statistical power of 0.9, a conservative effect size of 0.65 based on a previous systematic review with the average effect size calculated regarding the effect of exercise on executive function in children with ADHD [24], a two-tailed alpha level of 0.05, it is determined that 10 participants per group will provide adequate power to detect statistically significant differences. Assuming a 30% loss in the intervention, we will need to approach about 42 eligible participants to achieve the planned sample.

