### **Study Design**

A three-arm school-based randomized controlled trial (RCT) will be conducted to evaluate the effects of two different kinds of 12-week training programs on the executive function of children with ADHD. The design, conduct, and reporting for the RCT adheres to the guidelines of the Consolidated Standards of Reporting trials (<http://www.consort-statement.org/>) [54]. Participants will be randomly assigned to the GameHIIT group, the GameSAE group, or a non-treatment control group using a random number-producing algorithm (with a 1:1:1 allocation ratio within each school). A stratified random sampling procedure will be conducted that considers gender, IQ, and medication status. Raven's Standard Progressive Matrices (SPM) will be used to measure general intelligence. Equal numbers of boys and girls with similar general intelligence will be included in the three groups. Children taking medication will be equally distributed to the three groups. Participants will not be blinded to treatment allocation because of the intervention nature. To avoid contamination between treatment groups, intervention deliverers will be provided with a list of students in the intervention program. Only those on the list can participate in the intervention. During the 12-week intervention period, participants in the control group will maintain their regular PA levels. For ethical reasons, a cross-over study design will be adopted. That is, participants in the control group will receive either GameHIIT intervention or GameSAE intervention according to their preference after a 12-week formal intervention period. Accordingly, participants in the other two groups will have another 12-week follow up. Therefore, it is expected that all participants in the three groups will benefit from the proposed study. The flow diagram of the study design is shown in **Figure 1**.

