### **Statistical analyses**

Statistical analyses of the primary and secondary outcomes will be conducted with the IBM SPSS Statistic for Windows, Version 20.0 (2010 SPSS Inc., IBM Company Armonk, NY). Intervention effects for the primary and secondary outcomes will be examined by two-way (trial × time) analysis covariance (ANCOVA), including group as a fixed factor, pre-post intervention difference (change) as the dependent variable, and age, attendance, sports skill, and ADHD symptoms as covariates. Effect sizes (ES) will be presented as partial eta squared values ( $\eta^2$ ). Pairwise comparison will be performed (post-hoc) with Bonferroni correction, with ES presented as Cohen's *d*. Correlational analysis will also be conducted to evaluate the relationship between the changes in executive function and the fNIRS measures. All data will be presented as mean ± SD, and significance will be set as  $p < 0.05$  for all data analysis.

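### The stated 90% power with 10 children per group at effect size 0.65 does not follow from the stated inputs; read as a standardised mean difference, power against control is about 28%

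*Protocol*

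**What the plan says.** The Sample Size Calculation in the protocol uses G*Power 3.1. The target is set "with a statistical power of 0.9", with "a two-tailed alpha level of 0.05" and "a conservative effect size of 0.65 based on a previous systematic review with the average effect size calculated". The conclusion reads: "it is determined that 10 participants per group will provide adequate power to detect statistically significant differences". Recruitment is then set at about 42 to allow for 30% loss. The section does not name the test, the effect-size metric, the contrast or a pre-post correlation.

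Three other parts of the protocol bear on the figure:

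- The closing paragraph of the Background hypothesises that each of the two exercise programmes improves executive function relative to control. It adds a tentative secondary hypothesis that GameHIIT may do better than GameSAE.
- Study Design allocates three arms "with a 1:1:1 allocation ratio within each school".
- Statistical analyses takes the pre-to-post change as the dependent variable, with age, attendance, sports skill and ADHD symptoms as covariates. The baseline value of the outcome is not among them. "Pairwise comparison will be performed (post-hoc) with Bonferroni correction", and the pairwise effects are to be reported as Cohen's d.

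**The concern.** A standardised difference of 0.65 is of medium-to-large size, and ten children per arm is far below what a two-arm comparison needs to detect it with 90% power. The protocol gives a power, an effect size, an alpha and a resulting number that do not fit together. This is a wrong statement, not a detail left for the statistical analysis plan.

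The calculation is the protocol's only justification for the sample size, and it concerns the primary outcome. If the true effect equals the planning value, the trial would more likely than not miss it. A reader would then take a non-significant result as coming from a trial with 90% power, and so as fair evidence that exercise does not help.

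**Working it through.** **Inputs.** Effect size 0.65, two-sided alpha 0.05, target power 0.90, 10 per group after loss and 14 per group recruited (42/3), all from Sample Size Calculation and the 1:1:1 allocation in Study Design. The contrast is each exercise arm against control, from the Background hypothesis. Pre-post correlations are my assumption, because the protocol gives none.

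**Trying to reproduce 10 per group: 0.65 as a standardised mean difference d.** For a two-sample t test the noncentrality is d × √(n/2), with 2n − 2 degrees of freedom.

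- At n = 10: 0.65 × √5 = 1.453, against a critical t of 2.101 on 18 df. Power is 28.0% (28.9% if the error variance is pooled over all three arms, 27 df).
- At n = 14: 0.65 × √7 = 1.720. Power is 38.1%.
- For 90% power, 50 per arm falls just short (89.6%) and 51 per arm gives 90.2%.
- Sensitivity at alpha 0.05/3 = 0.0167: 14.6% at n = 10 and 22.1% at n = 14; 90% needs 66 per arm.
- The omnibus three-group test, with both exercise arms 0.65 SD above control, has f = 0.65 × √2/3 = 0.306. Its power at N = 30 is 27.6%.

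A one-sided test (40.3%), a paired within-group test (45.1%) and both exercise arms pooled against control (20 versus 10, 36.7%) do not reach 90% either.

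**Trying to reproduce 10 per group: 0.65 as Cohen's f.** For a one-way ANOVA with three groups, λ = f² × N = 0.4225 × 30 = 12.675 on 2 and 27 df. Power is 86.3%. Reaching 90% needs N = 34, or 36 with equal groups.

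**Settings that do land near 30.** All need inputs that the protocol does not state:

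| Test | Assumed settings | N for 90% |
|---|---|---|
| Repeated-measures interaction, 3 time points | f = 0.325, correlation 0.5 | 27 |
| Repeated-measures interaction, 2 time points | f = 0.325, correlation 0.6 | 28 |
| Repeated-measures between-group test | f = 0.65, correlation 0.5 to 0.8 | 24 to 31 |
| ANCOVA, numerator df 1 | f = 0.65 | 28 |

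**Which reading is better supported.** The value comes from a systematic review in which an average effect of exercise was calculated, and pairwise effects are to be reported as Cohen's d. Both point to d. If the two exercise arms are equally effective, f = 0.65 would mean a difference from control of 0.65 × 3/√2 = 1.38 SD. The Background puts long-term exercise effects at no more than 0.96. Even with a 1.38 SD difference, pairwise power at 10 per arm is 83% at alpha 0.05 and 67% at 0.0167.

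**Power of the planned change-score comparison.** If d is expressed in raw-score SDs and r is the pre-post correlation, the SD of change is √(2(1 − r)) raw SDs, so the effective difference is 0.65/√(2(1 − r)). For 10 per arm, two-sided alpha 0.05 and 18 df, the difference detectable with 90% power is 1.534 SDs of the variable analysed. This gives:

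| Assumed r | SD of change | Effective difference | Power | Detectable with 90% power (raw SD) |
|---|---|---|---|---|
| 0.5 | 1.000 | 0.650 | 28% | 1.53 |
| 0.7 | 0.775 | 0.839 | 43% | 1.534 × 0.775 = 1.19 |
| 0.8 | 0.632 | 1.028 | 58% | 1.534 × 0.632 = 0.97 |

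Reaching 90% would need r of about 0.91, from 1 − (0.65/1.534)²/2. These figures leave out any precision gained from the listed covariates, for which the protocol gives no value.

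**The case against.** The strongest reply is that the section names no test, so 28% depends on a choice the sponsor may not have made. Statistical analyses describes a group-by-time analysis and makes the pairwise comparisons post hoc, so an omnibus interaction is close to the written primary test, and common software settings for such a test return about 30 children.

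Much of this stands. It cannot be said that no calculation gives 10 per group, nor that only a three-time-point analysis does: a two-time-point interaction also lands there, and it does not use the follow-up assessment at which controls have been offered treatment. The Bonferroni figures belong to the post-hoc step and assume three comparisons, while the primary hypothesis has two contrasts against control; they are a sensitivity result.

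The reply does not rescue the stated figure. An omnibus test has the same power, 27.6%, when both exercise arms differ from control by 0.65 SD. The routes to 30 rest on a metric, a correlation or a test that the protocol does not give.

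A reader might also infer three further errors that the protocol does not establish:

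- **Attrition.** 42 × 0.70 = 29.4 against 30 is less than one child, and the text says "Assuming a 30% loss in the intervention, we will need to approach about 42 eligible participants". This is rounding.
- **The word conservative.** The sentence says that 0.65 is based on a review in which an average was calculated. It does not plainly say that 0.65 is that average, so the label cannot be judged without the review.
- **GameHIIT against GameSAE.** This is a tentative secondary hypothesis and need not be powered.

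**Conclusion.** The point holds in this form: 10 per group for 90% power does not follow from the inputs given. On the best-supported reading, power for each exercise arm against control is about 28% at 10 per arm and 38% at 14 per arm, and 90% needs 51 per arm, about five times the stated number. On the alternative reading as f, a one-way ANOVA gives 86% at 30 children, closer but still short.

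The 28% assumes that 0.65 is a standardised mean difference and that the analysis gains no precision over a simple two-sample comparison. A high pre-post correlation would help: 43% at 0.7 and 58% at 0.8. Only a correlation of about 0.9 would bring the change-score comparison near 90%, and the protocol states none. It would go too far to quote 15% as the trial's power, or to claim that the sponsor used a particular wrong test.

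**What to change.** Keep the 42 children. In Sample Size Calculation, name the test, the effect-size metric, the contrast and any assumed pre-post correlation, and replace the claim of 90% or adequate power. Suggested wording:

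*With 10 children per arm completing the trial and two-sided alpha 0.05, the power of the change-score comparison of an exercise arm with control, for a difference of 0.65 SD, is about 28%, 43% or 58% if the pre-post correlation is 0.5, 0.7 or 0.8. The difference detectable with 90% power is about 1.5, 1.2 or 1.0 SD respectively. A non-significant result will not be taken as evidence of no effect; differences between arms will be reported with 95% confidence intervals.*

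These figures match the change-score analysis in Statistical analyses. Figures for a baseline-adjusted analysis should not be used in their place, because the baseline outcome is not a planned covariate. If the sponsor did use another test with its own settings, the protocol should state those settings and the difference from control that they imply.

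The cost is protocol wording, with no extra children. The downside is that the stated power becomes less favourable.
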